**Table 7 Summary of Adverse Events ARF-002**

Clinical outcomes for the 35 subjects enrolled are shown in Table 8. Death from any cause at Day 60 was 31.4%. This compares very favorably with the greater than 50% mortality reported in the literature [25] for subjects with similar SOFA scores.

Renal recovery was observed in all of the surviving subjects at Day 60. The mean time to ICU discharge from the beginning of SCD therapy was  $15.0 \pm 9.1$  days [CI 11.1,18.9] and the time to hospital discharge from the beginning of SCD therapy was  $21.8 \pm 10.9$  days [CI 17.0,26.6].

| Clinical Efficacy                                      | Outcome (N=35 Subjects)† | 95% CI        |
|--------------------------------------------------------|--------------------------|---------------|
| Primary Endpoint                                |                          |               |
| Death in hospital                                      | 28.6% (10/35)            | [14.6%,46.3%] |
| Death from any cause by day 28 from time of enrollment | 25.7% (9/35)             | [12.5%,43.3%] |
| Death from any cause by day 60 from time of enrollment | 31.4% (11/35)            | [16.9%,49.3%] |
| Other Clinical Efficacy                         |                          |               |
| Time to ICU discharge (days) from enrollment           | $15.0 \pm 9.1$ (23)      | [11.1,18.9]   |
| Time to hospital discharge (days) from enrollment      | $21.8 \pm 10.9$ (22)     | [17.0,26.6]   |
| No. of subjects discharged from ICU by day 28          | 60.0% (21/35)            | [42.1%,76.1%] |
| No. of subjects discharged from hospital by day 28     | 54.3% (19/35)            | [36.6%,71.2%] |
| No. of subjects discharged from ICU by day 60          | 65.7% (23/35)            | [47.8%,80.9%] |
| No. of subjects discharged from hospital by day 60     | 62.9% (22/35)            | [44.9%,78.5%] |
| Renal Recovery to day 28*                              | 73.1% (19/26)            | [52.2%,88.4%] |
| Renal Recovery to day 60*                              | 100% (24/24)             | [86.2%,100%]  |

† The presented numbers refer to: for discrete variable, % (no. patients with events/ total no. available patients) for continuous variable, Mean $\pm$ SD(N), where N is the number of available patients.

\*Does not include subjects who died (N=5 at day 28 and N=7 at day 60)

**Table 8 Clinical Efficacy Outcome ARF-002**

All safety data has been collected by the Clinical Research Organization (CRO), SAE and death notices are sent directly to CRO from the Principal Investigator with supporting source documentation. The CRO safety officer reviews this information, makes queries as necessary, and generates a narrative of the events for monthly safety reports that are sent to CytoPherx.

### **3. PIVOTAL STUDY (PROTOCOL SCD-003) OBJECTIVES AND ENDPOINTS**

#### **3.1. PRIMARY OBJECTIVE**

To achieve a clinically and statistically significant improvement on all-cause mortality through day 60 post randomization of CRRT + SCD treatment compared to CRRT alone

#### **3.2. SECONDARY OBJECTIVE**

To assess the effect of SCD treatment on various measures of patient clinical outcome, health economics and to evaluate the integrity of the SCD-ARF and patient safety in SCD treatments from the time of initiation of therapy to as many as seven consecutive 24-hour SCD treatments.

### **3.3. PRIMARY ENDPOINT**

The Primary Clinical Efficacy endpoint measure in this trial is time to all cause mortality through 60 day post randomization.

### **3.4. SECONDARY ENDPOINTS**

- Renal Replacement Therapy dependency at day 60.
- Mortality at day 28.
- Number of ventilator free days (VFD) at day 28.
- Mortality of Severe Septic patient sub-population at day 60.

Secondary Endpoints are defined in Appendix D.

## **4. STUDY DESIGN**

This is a two-arm, randomized, open-label, controlled multi-center Pivotal study.

## **5. SELECTION OF PATIENT POPULATION**

### **5.1. PATIENT RECRUITMENT**

Up to 30 Clinical Centers in the United States will enroll up to 344 patients to participate in this clinical trial. Patients receiving care in the Intensive Care Units of each participating hospital will be screened daily and identified for participation in the trial.

All patients that are screened for the study will be entered by the Study Staff on a screening log. If the patient is not enrolled, the screening log will include information explaining why enrollment did not take place (exclusion criteria, attending physician refusal, patient refusal, etc).

All enrolled patients will receive standard intensive care treatment for patients undergoing CRRT or CRRT + SCD. Any mode of CRRT will be allowed (CVVH, CVVHD, and CVVHDF) following each participating clinical site's protocol. The modality of CRRT is not expected to affect performance of the SCD.

The Sponsor will provide each site with a CRRT device (B.Braun Diapact® CRRT System) to be used with each patient randomized either to the Control or Study Arms. The B.Braun® CRRT System is a compact, self-containing system for high-flow continuous or intermittent renal therapies. Some of the technical features of the Diapact include an integrated plate warmer for the heating of infusion and dialysate fluids and a single load cell weighing system which reduces the possibility of error and increases accuracy. The Sponsor will also provide all the tubing, SCD-ARF and hemofilters to be used during the observation period of this trial.

Each participating clinical site is to use their regional citrate anticoagulation protocol for the CRRT and SCD-ARF circuits (Study Arm) and for the CRRT only (Control Arm). The recommended ionized calcium level (measured post

SCD-ARF) in the CRRT and SCD-ARF blood circuit should be between 0.25 and 0.4 mmol/L.

## 5.2. INCLUSION CRITERIA

1. A patient, or legal representative, has signed a written informed consent form.
2. Must be receiving medical care in an intensive care unit (e.g., ICU, MICU, SICU, CTICU, Trauma).
3. Age 18 to 80 years.
4. Females of child bearing potential who are not pregnant (confirmed by a negative serum pregnancy test) and not lactating if recently post-partum.
5. Must be receiving and tolerating CRRT for a minimum of 4 hours, but not longer than 24 hours.
6. Expected to remain in the ICU for at least 96 hours after evaluation for enrollment.
7. A clinical diagnosis of ATN due to hemodynamic or toxic etiologies. ATN is defined as Acute Kidney Injury occurring in a setting of acute ischemic or nephrotoxic injury with oliguria (average  $<20$  mL/hr) for  $>6$ – $12$  hours or: an increase in serum creatinine  $\geq 2$  mg/dL ( $\geq 1.5$  mg/dL in females) over a period of  $\leq 4$  days. (Note: Prerenal, hepatorenal, vascular, interstitial, glomerular, and obstructive etiologies are excluded on clinical or other diagnostic grounds.)
8. At least one non-renal organ failure (SOFA organ system score  $\geq 2$ ), as defined in Appendix A or presence (proven or suspected) of sepsis as defined in Appendix C.
9. All patients must be able to tolerate regional citrate anticoagulation.

## 5.3. EXCLUSION CRITERIA

1. Irreversible brain damage based on available historical and clinical information.
2. Presence of a renal transplant at any time.
3. Non-renal organ transplantation within six month of screening.
4. Presence of preexisting advanced chronic renal failure (Stage 5) prior to this episode of AKI. Preexisting Chronic Renal Failure is defined as a baseline serum creatinine  $>2.5$  mg/dL (men) or  $>2.0$  mg/dL (women).
5. AKI occurring in the setting of burns, obstructive uropathy, allergic interstitial nephritis, acute or rapidly progressive glomerulonephritis, vasculitis, hemolytic-uremic syndrome, thrombotic thrombocytopenic purpura (TTP), malignant hypertension, scleroderma renal crisis, atheroembolism, functional or surgical nephrectomy, hepatorenal syndrome, cyclosporine or tacrolimus nephrotoxicity.
6. Metastatic malignancy which is actively being treated or may be treated by chemotherapy or radiation during the subsequent three month period after study therapy.
7. Chronic immunosuppression (e.g., HIV/AIDS, chronic glucocorticoid therapy  $>20$  mg/day prednisone equivalent on a chronic basis). The acute use of glucocorticoids is permissible.
8. Severe liver failure as documented by a Child-Pugh Liver Failure Score  $>12$  (see Appendix F).
9. Do Not Resuscitate Status (DNR).

10. Comfort measures only.
11. Patient is moribund or for whom full supportive care is not indicated.
12. Patient is not expected to survive 28 days because of an irreversible medical condition. (This is not restrictive to AKI, and may include situations such as the presence of irreversible brain damage, untreatable malignancy, inoperable life threatening condition, or any condition to which therapy is regarded as futile by the PI.)
13. Any medical condition that the Investigator thinks may interfere with the study objectives.
14. Physician refusal.
15. Patient is a prisoner.
16. Dry weight >150 kg.
17. More than one hemodialysis treatment during this hospital admission or prior to transfer from an outside hospital.
18. Platelet count <30,000/mm^3.
19. Concurrent enrollment in another interventional clinical trial. Patients enrolled in clinical trials where only measurements and or samples are taken (NO TEST DEVICE OR TEST DRUG USED) are allowed to participate.
20. Use of any other interventional drug or device within the previous 30 days.

## **6. STUDY ACTIVITIES**

### **6.1. SCREENING PERIOD**

The screening period is the time period when a patient is identified, informed consent is obtained, and the patient is evaluated for inclusion in the clinical trial. Because of the critically ill nature of the study population, it is expected that the majority of patients will not be able to provide informed consent. Where subjects are unable to consent themselves, surrogate informed consent will be sought from the subject's healthcare proxy or other equivalent legal representative. Only adverse events directly related to the screening procedures will be reported during this time.

Medical history and test results must be analyzed to ensure the patient meets all eligibility criteria. Tests that are specific to this protocol (i.e. not standard of care) require the patient or legal representative to have provided written consent for participation.

Any patients that do not meet study criteria, whether consent was obtained or not, will not be randomized and enrolled into the study. These patients will not be counted in the overall study enrollment numbers, but will be listed on the screening log.

### **6.2. RANDOMIZATION**

A centralized randomization system has been established with 24-hour availability to provide a mechanism to randomize subjects and enroll them in the study. Once the patient meets all eligibility criteria, **including being on CRRT**

**for a minimum of 4 hours, but no longer than 24**, and has signed informed consent, the site will enter the patient into the randomization system.

Patients will be randomized in a 1:1 allocation utilizing a random permuted block design into either the control or treatment arm, stratified by study center and the presence of severe sepsis or not. (Appendix C). This should occur as close to the start of the Observation period as possible while also allowing time for baseline tests and data to be completed before the patient has been on CRRT for 24 hours. Patients will then be considered enrolled in the study and given a study number. Randomization results will not be revealed to the clinical team and patient until immediately prior to start of first treatment.

#### **6.2.1. CONTROL ARM**

Patients randomized to the control arm will receive renal replacement therapy utilizing a CRRT device that is identical to that used for the SCD treatment, tubing and hemofilter provided by the Sponsor. Anticoagulation of the system will be done using the institution's protocol for citrate anticoagulation. All patients in the control arm are required to use citrate as an anticoagulant.

#### **6.2.2. STUDY TREATMENT ARM**

Patients randomized to the study treatment arm will receive renal replacement therapy plus SCD using the CRRT device, first hemofilter, SCD-ARF, and all tubing provided by the sponsor. Anticoagulation of the CRRT and SCD system will be done using the institution's protocol for citrate anticoagulation. All patients in the treatment arm are required to use citrate as anticoagulant.

#### **6.3. BASELINE PERIOD**

The Baseline Period begins at randomization and ends at the start of the Observation Period. The following information will be recorded as close to the start of the Observation Period as possible. Data from standard of care tests may be used as baseline data, as long as it is captured within the time frames noted.

- **Demographic Data**
  - Date of birth
  - Gender
  - Race/ethnicity
- **Hospitalization Data**
  - Hospital Admission Date
  - Hospital Admission Diagnosis
  - ICU Admission Date
  - ICU Admission Diagnosis
- **Vital Signs/Physical Assessment**
  - Temperature
  - Blood Pressure, heart rate, body weight
  - EKG (**within 12 hours prior to the start of Observation Period**)
  - Sequential Organ Failure Assessment (SOFA Score)

- Physical Exam
  - Urine Output (previous 24 hours)
- **Clinical Laboratory Tests (within 12 hours prior to the start of Observation Period)**
  - CBC with differential
  - BUN/Creatinine
  - Na, K, Cl, HCO3, Ca, Mg, Ionized Ca, PO4
  - ALT, AST, LDH, Bilirubin, ALP, Total Protein, Albumin, Glucose
  - PT, PTT, INR
  - Haptoglobin
  - Urinalysis (if urine available)
- **Respiratory**
  - Status – Ventilator support (yes/no; date of intubation)
  - If on Vent: Mode, NO, FiO2, Settings (TV, PEEP, RR)
  - If on Vent with an arterial line: Arterial Blood Gas (12 hours prior to start of Observation Period)
  - If on Vent without an arterial line: Arterial Blood Gas (24 hours prior to start of Observation Period)
  - If not Vented: Supplemental oxygen requirements
- **Blood for Research**
  - Blood sample will be sent to an outside laboratory for testing of biomarkers such as IL6, IL10, Elastase, and GCSF.
- **Other (Event-driven)**
  - All the medications and blood products administered to the patient in the 24 hours prior to start of Observation Period.
  - Adverse Events occurring since randomization, unless directly related to screening procedure
  - Diagnostic/Therapeutic Procedures in the 24 hours prior to start of Observation Period.
  - Microbiology/culture data

#### **6.4. STUDY OBSERVATION PERIOD**

The Study Observation Period begins when the patient starts Control or Study Therapy and will continue up to a maximum of 168 hours from the time of Observation Start. It is expected that the patient will begin the Observation Period before the patient has reached 24 hours on CRRT.

This observation period has been broken into seven 24 hour time periods. It ends when the patient has reached 168 hours in the observation period or when the patient meets the termination criteria outlined in section 7.2 as determined by the Principal Investigator or Medical Team at the participating Clinical Site.

All tests are scheduled on a 24 hour cycle, or once a day, and can be scheduled to be drawn around each participating site's ICU blood drawing schedule, with the exception of any test that requires a specific draw frequency.

The following information will be obtained for patients enrolled in both study arms and recorded during the study observation period on a daily basis unless otherwise specified:

- **Vital Signs/Physical Assessment**
  - Temperature
  - Blood Pressure, heart rate – every 4 hours (+/- 1 hour)
  - Body weight
  - Sequential Organ Failure Assessment (SOFA Score)
  - Urine Output (previous 24 hours)
  - Net Fluid Balance (previous 24 hours)
- **Clinical Laboratory Tests**
  - CBC with differential – every 8 hours (+/- 2 hours)
  - BUN, Creatinine
  - Na, K, Cl, HCO3, Ca, Mg, Ionized Ca, PO4
  - ALT, AST, LDH, Bilirubin, ALP, Total Protein, Albumin, Glucose
  - Haptoglobin (on the last day of therapy only)
  - PT, PTT, INR
- **Respiratory**
  - Status – Ventilator support (yes/no; date of extubation)
  - If on Vent: Mode, FiO2, Settings- TV, PEEP, RR (q4h first 12 hrs (+/- 30 min) of observation period and then q12h (+/- 1 hour) thereafter)
  - If on Vent with an arterial line: Arterial Blood Gas (q4h first 12 hrs (+/- 30 min) and then q12h (+/- 1 hour) thereafter)
  - If on Vent without an arterial line: Arterial Blood Gas (once per 24 hours)
  - If not Vented: Supplemental oxygen requirements (q4h first 12 hrs (+/- 30 min) of observation period and then q12h (+/- 1 hour) thereafter)
- **Blood for Research**
  - Collect at hours 24, 72, 120, and 168 (+/- 4 hours). If study observation period ends prior to hour 168, collect at end of study observation period. Blood for biomarkers will be collected as close as possible to the time of SCD scheduled changes in the days required (+/- 4 hours) if practical.
  - Blood sample will be sent to an outside laboratory for testing of biomarkers such as IL6, IL10, Elastase, and GCSF.
- **CRRT Parameters (Both study arms – start at hour 0)**
  - Parameters include modality, blood flow rate, net fluid removal, dialysate or replacement solution flow rate, citrate infusion rate, calcium replacement rate (every 6 hours +/- 1 hour)
  - System performance (circuit survival - event driven)
  - Post filter ionized calcium (every 6 hours +/- 1 hour)
- **SCD Performance (Treatment Arm Only – start at hour 0)**
  - SCD-ARF performance (event driven)
- **Other (Event Driven)**
  - All the medications and blood products administered to the patient.

- Adverse Events
- Diagnostic/Therapeutic Procedures
- Microbiology/culture data

## **6.5. STUDY FOLLOW UP PERIOD**

### **6.5.1. POST END OF STUDY TREATMENT PERIOD**

This Study Follow Up period has been broken into seven 24 hour time periods. It starts when the patient has reached 168 hours in the observation period or when the patient meets the termination criteria outlined in section 7.2. It ends at 168 hours or until ICU discharge, whichever comes first. (Except for SOFA, net fluid balance and pressor use, which are followed until ICU discharge or Day 28, whichever comes first and microbiology/culture data which will be collected until hospital discharge or Day 60, whichever comes first.)

Record the following data daily in the Study Follow Up Period unless otherwise noted:

- **Vital Signs/Physical Assessment**
  - Blood pressure and heart rate
  - SOFA Score (record until ICU discharge or Day 28)
  - Physical Exam (first 24 hours only)
  - Body weight and temperature
  - EKG (first 24 hours only)
  - Urine Output (from previous 24 hours)
  - Net fluid balance (record until ICU discharge or Day 28 - from previous 24 hours)
- **Clinical Laboratory Tests (first 24 hours only)**
  - CBC with differential
  - BUN, Creatinine
  - Na, K, Cl, HCO3, Ca, Mg, Ionized Ca, PO4
- **Respiratory**
  - Status – Ventilator support (yes/no)
  - If on Vent: Mode, FiO2, Settings- TV, PEEP, RR
  - If on Vent with an arterial line: Arterial Blood Gas
  - If not Vented: Supplemental oxygen requirements
- **Renal Replacement Therapy status**
  - RRT status
- **Other (Event Driven)**
  - All the medications and blood products administered to the patient.
  - Pressor Usage (record until ICU discharge or Day 28)
  - Diagnostic/Therapeutic Procedures
  - Adverse Events
  - Microbiology/culture data (record until hospital discharge or Day 60)

### **6.5.2. DAY 28 POST RANDOMIZATION**

This visit may be done via telephone call or office visit. Please record the following information on day 28 (+7 days) following enrollment:

- Blood pressure, heart rate and temperature (if known)
- Presence of mechanical ventilation (since last visit)
- Presence of renal replacement therapy (since last visit)
- Adverse events (since last visit)
- Serum creatinine (if an office visit takes place)

### **6.5.3. DAY 60 POST RANDOMIZATION**

This visit may be done via telephone call or office visit. Please record the following information on day 60 (+7 days) following randomization:

- Blood pressure, heart rate and temperature (if known)
- Presence of mechanical ventilation (since last visit)
- Presence of renal replacement therapy (since last visit)
- ICU discharge date
- Hospital discharge date
- Adverse events (since last visit)
- Serum creatinine (if an office visit takes place)
- SF36v2 Quality of Life Questionnaire

## **7. TREATMENT INTERRUPTIONS – DISCONTINUATION CRITERIA**

### **7.1. TREATMENT INTERRUPTION CRITERIA**

The SCD is to be used continuously along with CRRT and changed every 24 hours or at anytime the circuit exhibits significant clotting that impairs the functionality of the circuit. For patients randomized to either arm of the study, each participating site will follow their institution's protocol or standard of care in regard to replacement of the CRRT hemofilter and/or tubing.

In the event that a procedure is needed (e.g. CT-Scan, MRI), the CRRT or CRRT+SCD treatments may be interrupted for a maximum of 6 hours (cumulative) per 24 hour period. Cumulative interruption of greater than 6 hours in either the treatment or control arm will trigger the end of Observation Period and immediate initiation of the Follow-up period. These patients will not be removed from the study unless consent is withdrawn.

### **7.2. TREATMENT DISCONTINUATION CRITERIA**

#### **7.2.1. CLINICAL CRITERIA**

Patients may be withdrawn from therapy (control or treatment) prior to hour 168 for a variety of reasons. When therapy is discontinued prior to hour 168, the follow-up period will immediately begin and data will continue to be collected per protocol.

The Principal Investigator will assign a primary reason for therapy termination utilizing the following categories, and if appropriate, one or more subcategories:

#### **1. Improvement in Clinical Status**

- If a patient's condition improves (e.g. renal condition has improved to the extent that CRRT can be discontinued or hemodynamic status has improved so that the dialysis modality

can be changed from CRRT to IHD) treatment may be discontinued before the 168 hour treatment period. The decision to discontinue treatment based upon improvement in clinical status will be made by the Principal Investigator.

**2. CRRT related medical events**

- Such as persistent leukopenia, neutropenia or thrombocytopenia based upon PI's clinical assessment of relationship to control arm.

**3. SCD related medical events**

- Such as persistent leukopenia, neutropenia or thrombocytopenia based upon PI's clinical assessment of relationship to SCD.

**4. CRRT Failure/Malfunction**

- Failure of the CRRT device and/or circuit, including inability to maintain vascular access that requires treatment to be discontinued prior to hour 168 of therapy.

**5. SCD Failure/Malfunction**

- Any failure of the SCD-ARF that requires treatment to be discontinued prior to hour 168 of therapy—e.g. clotting or evidence of leakage in the SCD-ARF or inability to maintain a patent circuit.

**6. Death, including withdrawal of life support**

**7. Concomitant Medical Conditions**

- Need for medical, surgical or diagnostic procedures that necessitate discontinuation of CRRT or CRRT + SCD treatment for longer than the allowable 6 hours per 24 hour period.

**8. Other**

- Any other reason that the Principal Investigator deems appropriate for discontinuation from the Study Observation period must be documented.

**7.2.2. NON-CLINICAL**

**• Withdrawal of participation from study observation period**

Patients may withdraw their consent to participate in the study observation period (CRRT or CRRT + SCD) at any time. If the patient wishes to remain in the clinical study, the follow-up period will immediately begin at the termination of study observation period. All data will continue to be collected per protocol.

The Principal Investigator will notify the Sponsor's Chief Medical Officer or designee within 24 hours of withdrawal of consent.

- **Withdrawal of consent**

If a patient or legal representative withdraws consent, all protocol related activities will be immediately discontinued. If study therapy (CRRT+SCD) is being administered at the time of withdrawal, normal procedures will be followed for CRRT+SCD therapy discontinuation (please see SCD Operator's Manual). No further study activity will be conducted.

The Principal Investigator will notify the Sponsor's Chief Medical Officer or designee within 24 hours of withdrawal of consent.

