#### 12.5. PRIMARY ENDPOINT

The primary endpoint in this trial is time to mortality through 60 days post-randomization. The Kaplan-Meier curve of time (days) to mortality through 60 days post-randomization will be presented, as will the Kaplan-Meier estimate of the 60 day mortality rate. In addition, the raw number and percentage of subjects who died by 60 days will be presented by treatment group. Treatment groups will be compared on time to mortality through 60 days using the log-rank test. The analysis will be carried out for the ITT (primary) and Per-Protocol (secondary) analysis set. It is anticipated there will be few randomized subjects who prematurely withdraw from the trial. Subjects who do not die will be censored at 60 days or at the last known time alive, whichever is earlier.

Due to one formal interim efficacy analysis following which the DSMB may recommend an increase in sample size (based on the observed treatment difference seen at the interim analysis) beyond the initially planned 172 randomized patients (see Section 12.8 for details), the final analysis comparing treatments on the primary endpoint does not use the conventional log-rank test p-value to determine if a statistically significant treatment difference exists. Instead it uses a weighted test statistic,  $T^*$ , proposed by Cui, Hung and Wang [33] in which the independent test statistics of the two stages (interim and final) are combined by pre-specified weights,  $w_1$  and  $w_2 = 1 - w_1$ , where  $w_1$  is the proportion of the total *initially* planned number of patients at which the interim analysis is performed. In the present case the trial is designed for 172 randomized subjects per group with an interim analysis after 50% of the patients achieve 60 day follow-up (or would have achieved 60 day follow-up had they not died or prematurely withdrawn). Thus, the planned information time proportions are  $w_1 = 50\%$  for first stage and  $w_2 = 1 - w_1 = 50\%$  for the second stage.

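### Full withdrawal of consent ends collection of vital status, so a withdrawn patient is censored in the primary 60-day mortality test and no later analysis can recover the outcome

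*Protocol*

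**What the plan says.** Section 7.2.2 gives two ways out for non-clinical reasons. A patient may leave the treatment and observation phase only: "If the patient wishes to remain in the clinical study, the follow-up period will immediately begin at the termination of study observation period", and data collection goes on. Or consent itself is withdrawn: "If a patient or legal representative withdraws consent, all protocol related activities will be immediately discontinued", and after that "No further study activity will be conducted". Nothing lies between the two, and the second has no exception for survival status.

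Section 9.7.2 records serious adverse events to day 60 but stops earlier if study consent is withdrawn. Death counts as such an event under 9.2, so this route to a death also closes at withdrawal.

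Section 12.5 fixes the consequence for the primary log-rank test: "Subjects who do not die will be censored at 60 days or at the last known time alive, whichever is earlier". It also plans a secondary ITT analysis that imputes mortality status for patients who left early. That analysis uses multiple imputation by logistic regression on baseline characteristics, with 10 data sets, at the final analysis only.

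On setting, section 4 states: "This is a two-arm, randomized, open-label, controlled multi-center Pivotal study". Section 6.1 states that "it is expected that the majority of patients will not be able to provide informed consent", so consent at entry will often come from a representative. Section 12.2 expects attrition to be minimal and randomizes 172 per group for 166 evaluable.

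**The concern.** The log-rank test and the Kaplan-Meier estimates are valid only if censoring carries no information about prognosis. A family may withdraw consent because the patient is getting worse. Such a patient would be censored shortly before a death that belongs in the endpoint. Because treatment is known, the reasons for withdrawing could differ between arms, and then the comparison itself would be biased and not only the mortality level in each arm.

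The imputation does not protect against this. It predicts the outcome from baseline data, which assumes that withdrawal is unrelated to death once baseline is accounted for. It takes no account of what happened after randomization. It is also absent from the interim look, where the Kaplan-Meier difference drives the sample-size formula and the sign of that difference permits a futility recommendation (12.8). The secondary mortality endpoints are also censored at withdrawal (12.6).

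The gap is one of data collection. A statistical analysis plan can change how missing deaths are handled, but it cannot supply deaths that the protocol does not allow to be collected.

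**Working it through.** **Inputs (12.2).** Daily hazards 0.01155 and 0.00718, giving 60-day mortality of 50% and 35%, mean 42.5%. Power 80%, final two-sided level 0.049 (z = 1.969). 166 evaluable and 172 randomized per group.

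**The plan's own figure.** Hazard ratio = 0.00718/0.01155 = 0.6216, log = −0.4754. Deaths needed = 4 × (1.969 + 0.842)² / 0.4754² = 140. Per group = 140/(2 × 0.425) = 164.7. With an assumed O'Brien-Fleming inflation of 1.008 this is 166, so the stated number reproduces. The allowance is 172 − 166 = 6 per group, or 6/172 = 3.5%.

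**Power.** With vital status for all 344 patients: about 146 deaths, power 81.7%. With 166 per group: about 141 deaths, power 80.4%. Lost power is not the issue.

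**Margin for significance.** SE = √(2 × 0.425 × 0.575/172) = 0.0533. 1.969 × 0.0533 = 0.105, that is 10.5 points, or about 18 deaths in 172.

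**Extreme case at the planned allowance.** Assume that all 6 losses per group are withdrawals censored at once. Kaplan-Meier in effect gives them the mortality of those who remain. If all 6 in one arm in fact die and all 6 in the other survive, the two errors add:

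- at 42.5% in both arms: 6/172 × (0.575 + 0.425) = 3.5 points, one third of 10.5;
- at 35% on SCD and 50% on control, with the SCD losses dying: 6/172 × (0.65 + 0.50) = 4.0 points, about two fifths.

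**Less extreme cases.** Assume no true effect (50% in both arms), immediate censoring, and loss in the SCD arm only:

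| Lost, SCD vs control | Share of lost who die | Observed SCD mortality | Spurious benefit |
|---|---|---|---|
| 6 of 172 vs 0 | 75% | (86 − 4.5)/166 = 49.1% | 0.9 points |
| 6 of 172 vs 0 | 100% | (86 − 6)/166 = 48.2% | 1.8 points |
| 10% vs 0 | 75% | (0.50 − 0.075)/0.90 = 47.2% | 2.8 points |
| 10% vs 0 | 100% | (0.50 − 0.10)/0.90 = 44.4% | 5.6 points |

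Equal loss with equal risk in both arms gives a difference of 0.

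**Interim (12.8), illustration.** If 3.5% of controls withdraw early and all die, observed control mortality is 48.2% instead of 50%. The effect falls from 15 to 13.2 points, and the formula gives (15/13.2)² × 172 = about 222 instead of 172. Here the distortion works against SCD, so the direction is not fixed in advance.

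**The case against.** The strongest reply is that the rule is a defensible reading of consent, that few patients are expected to leave, and that the protocol already limits the damage. Patients who stop study treatment stay in follow-up (7.2.1). Withdrawal of life support is listed there under death as a reason for ending therapy, so limiting care does not require anyone to withdraw consent. An imputation analysis is planned. The consent form and the analysis plan are not shown and may say more. All of this lowers the likely number of affected patients. It does not open a route to vital status once consent is fully withdrawn.

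Several stronger readings are tempting, and the protocol does not support them.

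- A reader might infer that deaths are missed because the day-28 and day-60 lists have no survival line. For patients still in the study this does not follow. Death is a serious adverse event, reportable within 24 hours of the site learning of it in both arms, and both lists include "Adverse events (since last visit". It is true of day 60 that "This visit may be done via telephone call or office visit", but nothing bars a site from using hospital records or next of kin.
- A reader might infer that most withdrawals will be made by surrogates. Section 6.1 concerns who consents at entry; the protocol does not say who withdraws, how often or why.
- A reader might set all 12 planned losses against the 18-death margin and call it two thirds. The losses are 6 in each arm, so the extreme shift is about 6 deaths in 172, one third. The allowance also covers attrition in general and is not a count of withdrawals.

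**Conclusion.** The point holds in a limited form. Full withdrawal of consent closes every route to the primary outcome, the patient is censored in the primary test, and the planned sensitivity analysis would not correct censoring that depends on events after randomization. Whether censoring will be informative, or differ by arm, cannot be known from the protocol.

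At the planned allowance the shift is at most about 3.5 points (4.0 at the design mortality rates) against a margin of 10.5. More plausible one-sided cases give 0.9 to 1.8 points. It would matter if the result were close to the boundary or if withdrawal exceeded the allowance. These sizes assume immediate censoring, and the split between arms and the death rate among withdrawn patients are also assumed. This is a cheap improvement worth making, and it does not invalidate the design.

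**What to change.** In 7.2.2 add a third level: no further participation, but vital status through day 60 may be obtained. Offer it to the patient or representative at the time of withdrawal, and write it into the consent form where law and the IRB allow. Align 9.7.2 so that a death can be recorded for a patient at this level.

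Unless the analysis plan already has one, add a final sensitivity analysis that does not assume missing at random. A tipping-point analysis would serve: vary the assumed deaths among withdrawn patients separately by arm, and report where the conclusion changes.

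An explicit item for vital status and date last known alive at days 28 and 60 (6.5.2, 6.5.3, Appendix I) would be a useful form change, because the censoring rule in 12.5 needs that date. It is secondary to the change in 7.2.2.

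The cost is protocol and consent wording, IRB review, and record checks for about a dozen patients if losses match the allowance. Some representatives will still refuse, so the sensitivity analysis is needed in any case.
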